### Statistical analysis

The primary analysis will follow the intention-to-treat principle in the full analysis set that includes all randomised patients as belonging to their randomised arm, regardless of the treatment received or whether protocol violations occurred. The test on group difference regarding the time to the primary outcome will be performed based on a Cox regression model including the treatment group, age, stroke severity and country. To account for the adaptive design of the trial, the inverse normal method (with weights of $\sqrt{0.5}$ for stages 1 and 2, respectively) is applied to the Cox regression analyses on stage-wise data^18^ at overall 1-sided significance level of 2.5% using O’Brien and Fleming type α-spending function. Safety analyses will be performed for all patients for whom one of the treatments was started. Rates of adverse events will be calculated by treatment group, according to type of event and system organ class. Secondary endpoints will be analysed descriptively, using regression models as appropriate for the respective type of data. Treatment effects will be calculated with 2-sided 95% CIs.

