**Study design:**

Early treatment of Atrial fibrillation for Stroke prevention Trial in acute STROKE (EAST-STROKE) is an international investigator-initiated, prospective, randomised, open, blinded endpoint assessment (PROBE) interventional multi-centre trial. Patients with acute ischaemic stroke and AF will be randomised within 4 weeks of stroke (1:1) to receive either early rhythm control and usual care or usual care alone. Usual care includes oral anticoagulation, rate control and treatment of cardiovascular conditions. Early rhythm control additionally comprises treatment with antiarrhythmic drugs, AF ablation or cardioversion. A minimum of 1746 participants will be randomised to observe 351 events. The adaptive design includes one interim analysis with sample size re-estimation after 50% of events.

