**Study endpoints:**

The primary outcome is a composite of first recurrent ischaemic stroke, haemorrhagic stroke, unclassified stroke, cardiovascular death or hospitalisation due to worsening of heart failure or due to acute coronary syndrome, analysed as time to the first occurrence. Secondary outcomes include individual components of the primary outcome, functional status and patient-reported outcome measures. Safety outcomes comprise all-cause mortality and adverse events. Patients will be followed-up until the end of the trial with a minimum follow-up period of 24 months and an expected mean follow-up period of 42 months.

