### Treatment

EAST-STROKE is a comparative effectiveness trial that compares 2 treatment strategies in patients with acute ischaemic stroke and AF: usual care alone versus usual care and early rhythm control. All treatments (pharmacotherapy, cardioversion, ablation therapy) follow current standards and local practice with approved drugs and devices; no unapproved treatments are used. Individual treatment decisions, to achieve the randomised treatment aims, will be made by site teams.

The control arm follows standard AF management, which includes OAC, rate control and therapy of cardiovascular conditions in line with national and international guidelines. Anticoagulation therapy typically includes direct oral anticoagulants, vitamin K antagonists or other approved agents, eg, low-molecular-weight heparin, with initiation and monitoring following local protocols. Rate control, a primary approach in usual care, involves beta-blockers, calcium channel antagonists or digitalis glycosides. Dosing is adjusted to maintain a resting heart rate within a clinically acceptable range, typically below 100 or 110 beats per minute, with close monitoring for bradycardia or AF-related cardiomyopathy. Cardiovascular comorbidities will be managed according to standard practice without differences between randomised groups.^15^ Rhythm-control therapy in the usual care group follows local practice and is typically reserved for patients with persistent symptoms despite rate control.

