Patients in the intervention arm will receive early rhythm control as soon as possible after randomisation. Rhythm-control therapy includes antiarrhythmic drugs (mainly amiodarone, dronedarone, flecainide, propafenone), cardioversion, ablation or any combination of these 3 approaches, following local practice. We expect that antiarrhythmic drugs will be the primary means of starting early rhythm-control therapy, selected based on safety and standard practice. For long-term rhythm control, antiarrhythmic drugs, AF ablation or both can be used. When performed, AF ablation aims at pulmonary vein isolation following standard recommendations. Patients randomised to early rhythm control should be initiated on antiarrhythmic drug therapy within 2 weeks after randomisation or undergo AF ablation within 8 weeks after randomisation. Patients unable to receive rhythm control safely within this period are not eligible. After randomisation, treatment continues as part of standard care, with follow-up conducted per protocol (Figure 1).

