### Safety outcomes

Assessment of safety will comprise all-cause mortality and adverse events with a special focus on serious adverse events related to the study intervention with special emphasis on proarrhythmia and complications due to interventions, and severe bleeding complications, ie, ICH and major bleeding.

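### All-cause mortality is analysed in a safety set conditioned on treatment start; what counts as started and how patients are grouped are unstated, and two of three readings favour rhythm control

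*Protocol article*

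**What the plan says.** The safety population is set in one sentence of the protocol article, under Statistical analysis: "Safety analyses will be performed for all patients for whom one of the treatments was started". Under Safety outcomes, "Assessment of safety will comprise all-cause mortality and adverse events", and the abstract agrees: "Safety outcomes comprise all-cause mortality and adverse events". No separate population is given for mortality.

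The same Statistical analysis section gives the primary analysis a different population, the "full analysis set that includes all randomised patients as belonging to their randomised arm, regardless of the treatment received".

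The strategies compared, under Treatment, are "usual care alone versus usual care and early rhythm control". By the abstract, "Usual care includes oral anticoagulation, rate control and treatment of cardiovascular conditions". Patients in the intervention arm "should be initiated on antiarrhythmic drug therapy within 2 weeks after randomisation or undergo AF ablation within 8 weeks after randomisation". The Treatment section adds that patients who cannot safely receive rhythm control in that period are ineligible, and that drugs are expected to be the main way of starting.

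Adverse event rates are to be given by treatment group. The article does not say whether that means randomised or actual treatment, and it does not define a start of treatment for either arm.

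**The concern.** Whether a treatment was started is known only after randomisation, so a set built on it is not protected by randomisation. Here the condition can also act differently in the two arms. Usual care (anticoagulation, rate control, cardiovascular therapy) is routine for these patients, and nearly all controls will have some of it. Rhythm control can begin up to 2 weeks (drug) or 8 weeks (ablation) after randomisation, in an open trial, soon after an acute stroke. A patient who dies or deteriorates in that interval may never start.

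What is at stake is the mortality comparison and, by the same route, serious adverse events and major bleeding. The intention-to-treat primary analysis does not close the gap, because among deaths it counts only cardiovascular ones. Non-cardiovascular death is seen only through all-cause mortality. The sample size section itself assumes competing events in 1% of usual care and 2% of rhythm control patients: 873 × 0.01 = 8.7 and 873 × 0.02 = 17.5. The article does not list what these events are. If they are mainly non-cardiovascular deaths, the numbers are small enough for a few lost deaths to matter.

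**Working it through.** The plan gives no figure for the size of the safety set or for mortality, so there is nothing to reproduce. The only plan input below is 1746 / 2 = 873 patients per group (Sample size calculation). Every mortality input is an assumption.

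**Step 1: what the sentence can mean**

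| Reading | Rhythm-control patient on usual care who dies before starting rhythm control | Effect on mortality comparison |
|---|---|---|
| A. Assigned treatment must have started | Dropped | Favours rhythm control |
| B. Any treatment started, grouped as treated | Counted under usual care | Favours rhythm control, more strongly |
| C. Any treatment started, grouped as randomised | Stays in rhythm-control arm | About zero |

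The article's wording does not choose between these.

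**Step 2: effect on the risk ratio**

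Let true mortality be *m* in both arms (true ratio 1), and let a fraction *e* of the rhythm-control arm die before starting.

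- Reading A: apparent ratio = [(m − e)/(1 − e)] / m
- Reading B: apparent ratio = [(m − e)/(1 − e)] / [(m + e)/(1 + e)]

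With m = 10% (87.3 deaths per 873):

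| e | Deaths affected | Reading A | Reading B |
|---|---|---|---|
| 0.25% | 2.2 | 0.977 | 0.956 |
| 0.5% | 4.4 | 0.955 | 0.914 |
| 1% | 8.7 | 0.909 | 0.835 |

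For e = 1%: under A, (87.3 − 8.73)/(873 − 8.73) = 78.57/864.27 = 0.0909, and 0.0909/0.10 = 0.909. Under B the control arm becomes (87.3 + 8.73)/(873 + 8.73) = 96.03/881.73 = 0.1089, and 0.0909/0.1089 = 0.835.

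Under A with other values of *m*, as *e* goes from 0.25% to 1%: 0.952 to 0.808 at m = 5%, and 0.986 to 0.943 at m = 15%.

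**Step 3: is that range of *e* plausible?**

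At constant hazard with two-year mortality *p*, deaths in *d* days = 873 × [1 − exp(−h·d/365.25)], where h = −ln(1 − p)/2.

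| p | 14 days | 56 days |
|---|---|---|
| 2% | 0.3 | 1.4 |
| 5% | 0.9 | 3.4 |
| 10% | 1.8 | 7.0 |

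For p = 10% this is 1.8/873 = 0.2% of the arm by 14 days and 7.0/873 = 0.8% by 56 days, so the range in Step 2 is of the right order at that mortality. At lower mortality *e* is smaller: for p = 5% it is 0.9/873 = 0.1% by 14 days and 3.4/873 = 0.4% by 56 days. These counts overstate *e* if most patients start well before the window closes. They understate it if mortality is higher soon after the stroke. They also leave out patients who deteriorate, never start and die later.

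**The case against.** The strongest reply is that the literal text points to reading C. Usual care belongs to both strategies, so a rhythm-control patient on anticoagulation has had one of the treatments started and stays in the set. The rule would then remove only patients who received nothing after randomisation, such as immediate withdrawals or deaths. That reading is available, and the bias under it is about zero if grouping is as randomised. Under the same literal reading with grouping as treated, however, early deaths move to usual care.

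A reader might infer three stronger things, and the article supports none of them.

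- **That patients leave the rhythm-control arm only.** This depends on an unstated definition of start. A control could also die or withdraw before any usual-care treatment begins.
- **That the weeks before start, or everyone with an early event, are left out.** Starting is a condition of membership. Nothing says that events count only from the start date, so a patient who has an event and then starts is included. Only those who never start are affected.
- **That the loss can be sized by counting primary events in the first 8 weeks.** Most component types of the primary outcome need not be fatal or prevent a start, and 8 weeks is the outer limit for ablation, whereas drugs are expected to be the usual first step.

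Other parts of the reply have some force. The eligibility statement should keep non-starters few, although it cannot prevent an event after randomisation. The primary analysis covers cardiovascular death and haemorrhagic stroke in all randomised patients, and a data safety monitoring board oversees the trial. A condensed article may also leave the definition of start and the grouping to the full protocol. But the population itself is stated here, it is not the full analysis set, and no exception is made for mortality.

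**Conclusion.** The point holds as a defect in a stated analysis population, not as a demonstrated one-arm exclusion. All-cause mortality is tied to a set conditioned on a post-randomisation event whose meaning and grouping are open. Two of the three readings bias mortality towards rhythm control, and the third makes the restriction almost idle.

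Under the assumptions of no true effect, 10% mortality, and deaths before start in 0.25% to 1% of the arm, the apparent ratio is about 0.98 to 0.91 if those patients are excluded. It is about 0.96 to 0.83 if they are moved to usual care. The document supplies none of these mortality inputs, so the figures show direction and order of size only. The primary result and the sample size are untouched.

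**What to change.** Replace the safety population sentence so that all-cause mortality, serious adverse events, intracranial haemorrhage and major bleeding are analysed in the full analysis set, by randomised arm, from the day of randomisation. Keep the treatment-started set as a supplementary analysis of treatment-related events. For that set, define what counts as started in each arm and state whether grouping is by randomised or actual treatment.

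The cost is one sentence and one extra table. No new data should be needed: the follow-up schedule runs from randomisation and asks about outcome and adverse events, with no stated limit to treated patients. Treatment-related event rates will be slightly diluted in the all-randomised table. If 2%, 5% or 10% never start (assumed), about 856, 829 or 786 of 873 rhythm-control patients were exposed, so such rates read as 98%, 95% or 90% of those among starters. The supplementary table shows the undiluted rates. If reading C was intended, the change costs almost nothing, because nearly the same patients are analysed.

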### Interim analysis

After 176 events, ie, 50% of the planned events, an interim analysis with the possibility to stop for efficacy or futility will be conducted. The significance level for a stop for efficacy is determined by an O’Brien and Fleming type α-spending function at overall 1-sided significance level of 2.5%. For futility stopping, a non-binding boundary (*P* ≥ .5) is defined. The sample size re-calculation will be based on conditional power using the treatment effect derived by the interim analysis.^19^

### Biomarker and imaging substudies

For a subgroup of patients, blood-based biomarkers will be studied in an accompanying scientific program to determine the association of cardiac and other biomarkers with cardiovascular outcome events and risk of recurrent AF in patients randomised to early rhythm control. Biomarkers will be measured at baseline and during follow-up at 24 months. For a subgroup of patients, brain imaging using MRI will be performed to study brain volume, morphology and vascular lesions at baseline and during follow-up at 24 months. Both baseline findings and changes occurring over time (eg, brain atrophy and silent new vascular lesions) will be studied in relation to treatment, cardiac rhythm throughout the trial, cognitive function and as surrogate imaging outcomes.

## Discussion

EAST-STROKE is an international, investigator-initiated, randomised controlled trial designed to assess the efficacy and safety of early rhythm control in patients with acute ischaemic stroke and AF. Despite the well-established role of OAC in preventing stroke in AF patients, the risk of recurrent stroke and major cardiovascular events remains substantial, even with optimal OAC. Given the high burden of AF-related strokes and their severe consequences, additional preventive strategies are needed.

Previous studies have suggested that maintaining sinus rhythm may offer further protection beyond OAC alone. However, prior rhythm-control trials focused on broader cardiology populations, and their applicability to acute stroke patients remains unclear. EAST-AFNET 4 demonstrated a significant reduction in cardiovascular events with early rhythm control in patients with recently diagnosed AF and cardiovascular comorbidities, but it did not specifically include patients with an acute ischaemic stroke.^9^ Subgroup analyses from EAST-AFNET 4,^17^ observational studies^11^ and a small pilot study^10^ indicate a potential benefit of rhythm control in stroke populations, supporting the hypothesis of EAST-STROKE. However, these findings require confirmation in a sufficiently powered trial.

EAST-STROKE will determine whether early rhythm control, in addition to usual care, reduces recurrent stroke and major cardiovascular events in patients with AF and acute ischaemic stroke. The trial incorporates a composite primary outcome, including recurrent ischaemic stroke, haemorrhagic stroke, unclassified stroke, cardiovascular death or hospitalisation due to heart failure or due to acute coronary syndrome, reflecting the broad spectrum of cardiovascular risks in this population.

EAST-STROKE is a therapy strategy trial delivering an innovative treatment concept, namely early rhythm control, using approved pharmacological and interventional therapies. The study’s adaptive design, including an interim analysis, permits an early stop for efficacy or futility. As part of the interim analysis, information from the current study population can be used to re-estimate the sample size more precisely, ensuring an adequate power.

Usual care in EAST-STROKE allows adaptation of acute stroke and AF management to new evidence emerging during the trial period in both study groups, thereby enhancing external validity and ensuring relevance to contemporary clinical practice.

Beyond clinical efficacy and safety, EAST-STROKE will assess functional outcomes, patient-reported health-related quality of life and cost-effectiveness. Given the disabling nature of recurrent strokes and the high healthcare burden associated with AF-related complications, understanding the broader impact of early rhythm control is crucial for guiding treatment decisions and healthcare policy. These clinical outcomes are complemented by brain MRI and blood biomarker substudies, enabling the exploration of novel risk markers, mechanistic pathways and additional clinically relevant outcomes.

## Summary and conclusions

EAST-STROKE is a therapy strategy trial delivering an innovative treatment concept, early rhythm control using approved therapies, in patients with acute ischaemic stroke and AF. The trial will provide evidence on whether early rhythm control, in addition to usual care, is safe and effective in preventing recurrent stroke and other major cardiovascular events compared to usual care alone. The EAST-STROKE trial addresses an unmet need and has the potential to improve outcomes for patients with AF and acute ischaemic stroke. Its findings will provide important evidence for clinicians, researchers and policymakers.
